### Primary objective, outcomes, and hypotheses

The primary objective of the FFW effectiveness trial is to provide the first investigation of the effectiveness of FFW to increase well-being and physical activity in adults with obesity in the USA. Primary outcomes in the FFW effectiveness trial are: well-being self-efficacy, subjective well-being and well-being actions. These three constructs were chosen as primary outcomes based on some results from the 2015 FFW efficacy trial and the availability of at least some validity evidence for the relevant instrumentation (WBSE, I COPPE and I COPPE actions scales) prior to data collection. Three construct-level a priori hypotheses are listed below.The FFW intervention will exert a positive direct effect on well-being self-efficacy.The FFW intervention will exert a positive direct effect on subjective well-being.The FFW intervention will exert a positive direct effect on well-being actions.

One construct-level exploratory hypothesis also will be investigated based on the conceptual model depicted in Fig. 2 and consistent with suggestions for future research on the FFW intervention [1, 26].

1.The FFW intervention will exert a positive indirect effect on subjective well-being through well-being self-efficacy

Dimension-specific hypotheses for primary outcomes were not made due to a lack of previous research on the effectiveness of the FFW intervention.

### Secondary outcomes and hypotheses

Secondary outcomes in the FFW effectiveness trial are: well-being actions self-efficacy, physical activity self-efficacy, self-efficacy to regulate physical activity, and physical activity. These four constructs were chosen as secondary outcomes because validity evidence for the relevant instrumentation was not available prior to data collection and/or because they were not included in the 2015 FFW efficacy trial. Four construct-level a priori hypotheses with the intervention are listed below.The FFW intervention will exert a positive direct effect on well-being actions self-efficacy.The FFW intervention will exert a positive direct effect on physical activity self-efficacy.The FFW intervention will exert a positive direct effect on self-efficacy to regulate physical activity.The FFW intervention will exert a positive direct effect on physical activity.

Two construct-level exploratory hypotheses also will be investigated based on the conceptual model depicted in Fig. 2 and consistent with suggestions for future research on the FFW intervention [31].The FFW intervention will exert a positive indirect effect on well-being actions through well-being actions self-efficacy.The FFW intervention will exert a positive indirect effect on physical activity through physical activity self-efficacy and self-efficacy to regulate physical activity.

Dimension-specific hypotheses for secondary outcomes were not made due to a lack of previous research on the effectiveness of the FFW intervention.

## Methods/design

### Ethical approval

Each procedure in the current study that involves one or more human participants will be in accord with both the 1964 Helsinki declaration and its later amendments or comparable ethical standards and with the ethical standards of the institutional and/or national research committee. The University of Miami’s institutional review board provided needed authorization to conduct this study on 11 July 2017, IRB# 20170541. Table 1 provides the Standard Protocol Items: Recommendations for Interventional Trials (SPIRIT) flow diagram. A populated SPIRIT checklist is provided in the Appendix within Additional file 1.

**Table 1 Tab1:** SPIRIT flow diagram for the FFW effectiveness trial

	STUDY PERIOD					
	Enrolment	Allocation	Post-allocation			Close-out
TIMEPOINT**	***-t*** _***1***_	**0**	***t*** _***1***_ ***day 0***	***t*** _***2***_ ***day 30***	***t*** _***3***_ ***day 60***	***t*** _***x***_
ENROLMENT:						
Eligibility screen	X					
Informed consent	X					
Allocation		X				
INTERVENTIONS:						
*Fun For Wellness*			X	X		
*Usual Care*			X	X	X	
ASSESSMENTS:						
*Gender*			X			
*Age*			X			
*Race*			X			
*Education-level*			X			
*Marital status*			X			
*Annual income*			X			
*Zip code*			X			
*Height*			X	X	X	
*Weight*			X	X	X	
*Self-efficacy to comply*			X			
*Well-being self-efficacy*			X	X	X	
*Well-being actions self-efficacy*			X	X	X	
*Physical activity self-efficacy*			X	X	X	
*Self-efficacy to regulate physical activity*			X	X	X	
*Subjective well-being*			X	X	X	
*Well-being actions*			X	X	X	
*Physical activity*			X	X	X	
*Fun For Wellness Experience Survey*				X		

### Informed consent

Each eligible individual who wishes to be a participant in the study will be required to provide informed consent. More precisely, immediately after being determined to be eligible for this study, each eligible individual will be directed to a web-based IRB-approved informed consent form. Each individual who clicks the “Consent to Participate” will be enrolled as a participant in the study. Each individual who clicks “Decline to Consent” will be denied access to the intervention.

### Study design

The study design is a large-scale, prospective, parallel group RCT. Recruiting, verification of eligibility, random assignment and collection of data will be conducted online. Data collection will occur at baseline (Time 1), 30 days (Time 2) and 60 days (Time 3) after baseline. The timeline for this study is similar to timelines used in other well-being [37] and physical activity interventions [5]. The probability of rejecting a truly false null hypothesis (i.e., statistical power) for every focal parameter was estimated a priori and each of these estimates will be provided in the Data Analytic Approach section.

#### Recruitment

Approximately 9 hundred participants will be enrolled in this study. Participants will be recruited through the SurveyHealth (http://www.surveyhealthcare.com/) company’s panel recruitment based on the eligibility criteria for this study. Partnering with a panel recruitment company is consistent with recruitment in previous research on FFW [26, 27] and with a movement toward larger and smarter approaches that promote physical activity [9].

#### Eligibility

There are five eligibility criteria for participation in this study. The first eligibility criterion is the ability to access the online intervention. This criterion will be assessed by asking each participant to confirm that he or she will have access to a technological device (e.g., smartphone) that can access the online intervention via a web browser throughout the study. The second eligibility criterion is living in the USA. This criterion will be assessed by asking each participant to confirm that he or she is living in the USA. A justification for this criterion is evidence for differences in the prevalence of physical activity in adults by country [7]. The third eligibility criterion is being an adult between 18 and 64 years old. This criterion will be assessed by asking each participant the year in which he or she was born. A justification for this criterion is that our target population is adults (i.e., 18–64 years) and not older adults (i.e., 65 years and above) based on evidence-based age groupings for global recommendations on physical activity for health [38]. The fourth eligibility criterion is a body mass index (BMI) ≥ 25.00 kg/m^2^. Our BMI criterion includes the overweight category (i.e., 25.00–29.99 kg/m^2^) as well as the obese category (i.e., ≥ 30.00 kg/m^2^) consistent with many interventions promoting physical activity in obese populations [5]. This criterion will be assessed by asking each participant his or her height and weight. A justification for this criterion is trying to promote physical activity in a population where very few individuals may meet public health guidelines for physical activity [4]. The final eligibility criterion is the absence of simultaneous enrollment in another intervention program promoting either well-being or physical activity. This criterion will be assessed by requiring each participant to confirm that he or she will not be enrolled in another formal intervention program promoting either well-being or physical activity during the FFW study period. A justification for this criterion is a reduction in the likelihood of confounding the results from the current study with results that may be due to enrollment in other programs. The short form of the international physical activity questionnaire (IPAQ; [39, 40]) and the physical activity readiness questionnaire [41] will also be included in the screener and responses to these instruments may be used for exploratory purposes.

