**Methods:**

The study design is a large-scale, prospective, parallel group RCT. Approximately 9 hundred participants will be randomly assigned to the FFW or Usual Care (UC) group to achieve a 1:1 group (i.e., FFW:UC) assignment. Participants will be recruited through an online panel recruitment company. Data collection, including determination of eligibility, will be conducted online and enrollment is scheduled to begin on 8 August 2018. Data collection will occur at baseline, 30 days and 60 days after baseline. Instruments to measure demographic information, anthropometric characteristics, self-efficacy, physical activity and well-being will be included in the battery. Data will be modeled under an intent to treat approach and/or a complier average causal effect approach depending on the level of observed engagement with the intervention.

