#### Data collection

Instruments to measure demographic information, anthropometric characteristics, self-efficacy, well-being and physical activity will be included in the battery. Data on literature-based demographic covariates of multidimensional well-being [43] will be collected at Time 1 and will include participant gender, age, race, education-level, marital status, and annual income. Zip code data will be collected as a proxy for a host of built environment factors that may be related to an individual’s level of physical activity [10]. Anthropometric data will be collected at all three time points and will be assessed by asking each participant his or her height and weight. Demographic, zip code, and anthropometric variables are collectively referred to as covariates from this point forward.

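### Year of birth cannot decide the 18–64 age criterion for the two boundary birth years, and the article describes no other age check before the one-click consent

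*Protocol article*

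**What the plan says.** The Eligibility section of the protocol article sets the criterion: "The third eligibility criterion is being an adult between 18 and 64 years old". It gives the reason that "our target population is adults (i.e., 18–64 years) and not older adults (i.e., 65 years and above", so both limits are deliberate. It then names the check: "This criterion will be assessed by asking each participant the year in which he or she was born". It mentions no month or day of birth, no age in completed years, and no rule for the boundary birth years.

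The Informed consent section describes the next step: "immediately after being determined to be eligible for this study, each eligible individual will be directed to a web-based IRB-approved informed consent form". After that, "Each individual who clicks the “Consent to Participate” will be enrolled as a participant in the study".

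Age appears in two other relevant places.

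- The Data collection section lists it among the demographic covariates that "will be collected at Time 1 and will include participant gender, age, race, education-level, marital status, and annual income". The SPIRIT flow diagram (Table 1) puts that assessment after screening, consent and allocation.
- The Recruitment section says participants come through the "company’s panel recruitment based on the eligibility criteria for this study", but describes no verification of age.

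The Methods part of the abstract gives the reference date: "enrollment is scheduled to begin on 8 August 2018".

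**The concern.** The article does more than state an age range. It also states the input from which the range will be judged, and that input cannot settle the question for everyone. The other four criteria do not have this problem: three are confirmed directly by the participant, and BMI is worked out from the height and weight it needs.

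The lower limit matters more, because it is also the line between an adult and someone under 18. Screening, consent and enrolment are all online and follow one another without a described pause, so a wrong age decision at screening would not be caught by any later step in the text before the person is enrolled. The Time 1 age item could reveal it, but only after allocation. The team would then have to decide what to do with a randomised, ineligible person in a trial whose Model A is intent-to-treat. At the upper limit the stake is smaller: some participants would fall outside the stated target population, or some eligible 64-year-olds would be turned away.

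**Working it through.** The plan gives no figure to reproduce here, so the check is calendar arithmetic.

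**Inputs from the article**
- Age range 18 to 64, with 65 and above excluded (Eligibility).
- Year of birth as the screening item (Eligibility).
- Enrolment start 8 August 2018 (abstract, Methods).
- About 900 participants (Recruitment).

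**Assumptions that the article does not give**
- Birthdays are spread evenly over the year.
- Participants are spread evenly over the birth years accepted.

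**Step 1: possible ages on 8 August 2018**

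| Birth year | Dates 1 January to 8 August (birthday reached) | Dates 9 August to 31 December (birthday not reached) |
|---|---|---|
| 2000 | 221/366 = 60.4%, aged 18 | 145/366 = 39.6%, aged 17 |
| 1953 | 220/365 = 60.3%, aged 65 | 145/365 = 39.7%, aged 64 |

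Every birth year from 1954 to 1999 lies wholly inside the criterion on that date, and every year outside 1953–2000 lies wholly outside it. The ambiguity is confined to these two years.

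**Step 2: other screening dates**

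On 1 October 2018, 24.9% of each boundary cohort has not yet had its birthday (17 or 64) and 75.1% has (18 or 65). The ambiguity disappears only on 31 December. The article gives no enrolment end date. If screening ran into 2019, the boundary years would move to 2001 and 1954; on 1 February 2019 the split would be 91.2% aged 17 or 64 and 8.8% aged 18 or 65.

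**Step 3: what each birth-year rule would do on the start date**

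- *Accept both boundary years.* Birth years 1953–2000 are 48 cohorts, and 900/48 = 18.75 per cohort. Seventeen-year-olds: 18.75 × 0.396 = 7.4. Sixty-five-year-olds: 18.75 × 0.603 = 11.3. That is about 7 and 11 per 900.
- *Reject both boundary years.* The eligible people lost are 0.604 of one cohort (aged 18) plus 0.397 of another (aged 64), about one cohort in all. The eligible range spans 47 years of age, so the loss is 1/47 = 2.1%, equivalent to 900/47 = 19 per 900.
- *Require year difference 18 to 64.* This accepts 2000 and rejects 1953, leaving 47 cohorts of 900/47 = 19.1. Seventeen-year-olds admitted: 19.1 × 0.396 = 7.6. Eligible 64-year-olds turned away: 19.1 × 0.397 = 7.6. That is about 8 of each.

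**Step 4: range for the even-spread assumption**

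Under the accept-both rule the counts scale with the share of participants in each boundary cohort. If a cohort is half as common as assumed (18.75/2 = 9.375), the counts are 9.375 × 0.396 = 3.7 and 9.375 × 0.603 = 5.7. If twice as common (37.5), they are 14.9 and 22.6. If the panel holds nobody aged 17, the first count is zero.

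**Step 5: after the fix**

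With date of birth, or a direct confirmation of being in range on the day, each person has one eligibility answer. The number of undecidable birth years falls from two to none. The sample size and the power figures in Table 2 do not change.

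**The case against.** A reader might infer that the plan lets minors enrol on their own consent. The article does not say so. It gives no acceptance rule for the boundary years, and a conservative cut-off that rejects both would admit no 17-year-old and no 65-year-old, at the cost of about 2% of eligible adults, whom an online panel could replace. This part of the objection stands: admission of minors is one possible implementation, not something the plan states.

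A reader might also infer that year of birth is the only age check. The article does not say that either. The panel company recruits on the eligibility criteria, and the approved consent form, which is not shown, may ask for confirmation of age. This stands too, so the point is limited to what the article describes.

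It can further be argued that exact screener wording belongs in the full protocol, that no age distribution is given to support any count, and that a boundary error made before allocation affects both arms alike. The last two are right, and they limit the size of the point. The first does not remove it: the article did choose to state the check, and the check as stated cannot apply the criterion. Even the conservative cut-off narrows the published age range without saying so.

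**Conclusion.** The point holds as a minor one. The stated check cannot decide eligibility for people born in 2000 or 1953 when screening takes place in 2018 before 31 December, and no birth-year cut-off removes the problem. On the start date, with an even age spread, the cost is about 7 seventeen-year-olds and 11 sixty-five-year-olds per 900 if both years are accepted, or about 2% of eligible adults turned away if both are rejected. The counts depend on the assumed age spread, the screening date and the unstated acceptance rule. A panel with few 17-year-olds would give fewer at the lower limit.

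The documents do not support the stronger reading that minors will be enrolled, or that no other safeguard exists. Nor does the point bear on the trial's conclusions: power and the effect estimates are essentially unaffected. It concerns the integrity of eligibility and consent.

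**What to change.** Before the consent form is shown, either have the screener ask date of birth and compute age on that day, or keep year of birth and add a direct confirmation that the person is at least 18 and under 65 today. Block access to consent outside that range, and describe the check in the Eligibility section. If the consent form or the panel company already confirms age, one sentence saying so is enough.

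The cost is one changed or added screener item and a line of amendment. Date of birth is slightly more identifying than year of birth; it can be converted to age and discarded, and the confirmation item avoids collecting it at all. Sample size, power and analysis stay as they are.

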#### Random assignment

Eligible participants will be randomly assigned to the intervention (i.e., FFW) or the wait-list control (i.e., UC) group via software code that is written to accomplish equal (i.e., balanced) allocations to the FFW and UC groups. Research staff will be blinded to participant group assignment. The outcomes assessor will be blinded to participant group assignment.

##### Usual care

Participants assigned to the UC group will be prompted to use the unique and secure log-in credentials they will be provided when they are screened for the study. These participants will be asked to conduct their lives as usual during the intervention period. The unique and secure log-in credentials will, however, provide them with access to a secure website to complete the Time 1 battery, Time 2 battery, and the Time 3 battery. Participants allocated to the UC group will have an opportunity to receive up to $30 worth of Amazon electronic gift cards. Specifically, at Time 1 they may receive $5 (for completing the Time 1 battery), $10 at Time 2 (for completing the Time 2 battery), and $15 at Time 3 (for completing the Time 3 battery). Participants in the UC group also will be given 1 month of 24 h access to the 152 BET I CAN challenges after data collection for the effectiveness trial is closed.

##### Fun for wellness

Participants allocated to the FFW group will be prompted to use the unique and secure log-in credentials they will be provided when they are screened for the study. These credentials will provide them with 30 days (i.e., from Time 1 to Time 2) of 24 h access to the 152 BET I CAN challenges, as well as access to a secure website to complete the Time 1 battery, Time 2 battery, and the Time 3 battery. These participants will have the opportunity to receive a total of $45 worth of Amazon electronic gift cards. Specifically, at Time 1 they may receive $5 (for completing the Time 1 battery), $10 at Time 2 (for completing both the Time 2 battery and 15 BET I CAN post-introductory challenges) plus $15 more at Time 2 (for completing both the Time 2 battery and 30 BET I CAN post-introductory challenges), and $15 at Time 3 (for completing the Time 3 battery). The remuneration plan at Time 2 is linked to completing post-introductory challenges in an effort to increase engagement with the intervention. In the 2015 FFW efficacy trial the remuneration plan at Time 2 for FFW participants was not linked to completing post-introductory challenges.

There are four introductory challenges that focus on orienting participants to the FFW online behavioral intervention (e.g., an overview of the organization of the website; a brief introduction to the characters that perform in the vignettes; etc.). Participants must complete these introductory challenges to be able to access to the subsequent 148 non-introductory challenges. The non-introductory challenges are ordered in the FFW website by the BET I CAN abbreviation. Participants will self-select which non-introductory challenges to engage with. Challenges engaged with by each participant will be logged by computer software to provide information for the FFW engagement scoring system. This logging of challenges engaged with by each participant will be possible because access to the FFW online behavioral intervention will require each individual to use their unique and secure log-in credentials.

The operational definition for engagement (or equivalently, compliance) with the FFW online behavioral intervention will adhere to the FFW engagement scoring system described in the main outcomes paper for the 2015 FFW efficacy trial [1]. Within the FFW engagement scoring system, the potential impact of completing a given non-introductory challenge is initially classified as low impact (7 participation points), moderate impact (14 participation points) or high impact (21 participation points). The operational definition of full participation will be guided by both methodological (e.g., the identification of a sufficient number of compliers) and substantive (e.g., an individual would have to engage with the FFW online behavioral intervention for approximately 2 h to earn enough participation points) concerns as recommended in the compliance literature [42]. The operational definition for full participation is earning at least 21 participation points.

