#### Model B in more detail

Model B will impose a latent class (with two classes) regression model with CACE estimation for each proposed outcome with measures taken at Time 2 and Time 3 as the dependent variables. The first class (i.e., Class 1) will be conceptualized as never-takers. The second class (i.e., Class 2) will be conceptualized as compliers. A dichotomous indicator of latent class (where 0 = non-compliers in the FFW group, 1 = compliers in the FFW group, and a missing value for participants in the UC group) will be generated. Compliance classification, modeled as a categorical latent variable, will be regressed on covariates. Covariates, the outcome at Time 1 and group allocation will serve as predictors of the outcome at Time 2 and Time 3 and these regression coefficients will be freely estimated in Class 1 and Class 2. The two direct effects from group allocation to the outcome at Time 2 and Time 3 will be fixed to 0 in Class 1 (i.e., the exclusion restrictions: γ_ntTime2_ = γ_ntTime3_ = 0), and will be estimated freely in Class 2 (i.e., γ_cTime2_, γ_cTime3_). The intercepts for the outcome at Time 2 and Time 3 will be estimated freely in each class. Covariance between the error terms for the outcome at Time 2 and Time 3 will be estimated freely in each class. The focal parameters will be the direct effects from group allocation to the outcome at Time 2 and Time 3 in Class 2 (i.e., γ_cTime2_, γ_cTime3_).

A positive focal parameter value will convey that compliers in the FFW group had a higher adjusted mean for the outcome as compared to potential compliers in the UC group.

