We are aware of at least four noteworthy limitations for this study. First, we acknowledge that there is some ambiguity concerning the utility of our operational definition of engagement (i.e., full participation). Although the operational definition of engagement in the current study will be consistent with previous research [1], we encourage continuing efforts to further understand engagement with the FFW intervention. Second, we recognize that our hypotheses assume additivity of FFW effects for all demographic covariates (i.e., no a priori moderators for the proposed effects of FFW). We encourage future secondary analyses that explore the prospect of heterogeneous FFW effects for sub-groups of individuals on well-being and/or physical activity. Third, we note that another limitation is that all of the data collected, except for engagement, will be collected via self-report. Future studies that collect proposed outcome data (e.g., well-being actions and physical activity) from more objective methods are encouraged. A final limitation is that the sample may be drawn from a somewhat broad population. Because recruitment for the study will occur via a partnership with a panel recruitment company, it is possible that a very heterogeneous sample may be enrolled. Subsequent studies that sample from a more narrowly defined population (e.g., adults with obesity who also suffer from a particular non-communicable disease) may provide different results.

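### Allocation comes before the self-reported Time 1 battery, so the baseline outcome adjusted for in Models A to C may already reflect knowledge of arm or early intervention content

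*Protocol article*

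**What the plan says.** **Order.** In Table 1 (Ethical approval section) allocation stands at timepoint 0. Day 0 (t1) is the first column under "Post-allocation", and every Time 1 outcome scale is marked there. Only the eligibility screen and consent fall under enrolment.

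The text gives the same order. In Usual care: "Participants assigned to the UC group will be prompted to use the unique and secure log-in credentials", and the Time 1 battery follows. In Fun for wellness (under Random assignment), the log-in of participants already allocated to FFW gives "30 days (i.e., from Time 1 to Time 2) of 24 h access to the 152 BET I CAN challenges", and the same sentence lists the Time 1 battery: "24 h access to the 152 BET I CAN challenges, as well as access to a secure website to complete the Time 1 battery". Informed consent and Eligibility place no primary outcome scale before allocation. The screener holds the eligibility items, the short IPAQ and a readiness questionnaire.

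**Knowledge of arm.** Random assignment says "Research staff will be blinded to participant group assignment" and says the same of the outcomes assessor, but does not mention participants. UC participants get their own instruction: "These participants will be asked to conduct their lives as usual during the intervention period". Gift cards total up to $30 in UC and $45 in FFW. By the Discussion, "all of the data collected, except for engagement, will be collected via self-report".

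**Use in the analysis.** Time 1 is called baseline. Model B in more detail states: "Covariates, the outcome at Time 1 and group allocation will serve as predictors of the outcome at Time 2 and Time 3". Model A does the same, and Model C inherits it from Model B.

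**The concern.** Adjusting for a baseline is safe because randomisation cannot have influenced a value recorded before it. Here the baseline is recorded afterwards. The primary outcomes are self-rated confidence, satisfaction and actions, and learning that one is in the programme or on a wait-list could plausibly move such answers.

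FFW participants may also have met intervention content by then. The self-efficacy-to-comply item is asked after the four introductory challenges, yet Table 1 marks it in the same day 0 column as the outcome scales.

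If the arms differ at Time 1 because of allocation, adjustment moves the estimated effect away from its true value. People may also leave between allocation and Time 1, at rates that may differ by arm.

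**Working it through.** The plan gives no figure on this point, and the Table 2 power values do not enter the check. The order is settled by reading Table 1 beside the Usual care and Fun for wellness sections. They agree, and no other section contradicts them. The arithmetic below only shows what could follow.

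**Inputs from the document.** Engagement of 25%, 45% or 65% and a complier effect of d = 0.20 (Statistical power estimation).

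**Assumed inputs.** A shift δ of 0.05 to 0.15 SD in Time 1 scores between arms, caused by knowing the arm, and a slope of 0.6 to 0.7 of the later score on the Time 1 score. The document gives neither.

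**Formula.** Let b be the score that would have been given before allocation, T the arm (FFW = 1), and γ the effect apart from the reaction to knowing one's arm. The recorded baseline is b + δT.

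- *The shift fades before follow-up.* The outcome is slope × b + γT. Replacing b by (recorded baseline − δT) makes the coefficient of T equal to γ − slope × δ. The error is −slope × δ, opposite in sign to the shift.
- *The shift persists fully.* The outcome is slope × b + γT + δT. The coefficient becomes γ + (1 − slope) × δ. The error has the same sign as the shift.

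**Numbers, in SD units**

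| Case | Smallest | Largest |
|---|---|---|
| Fades, −slope × δ | −0.6 × 0.05 = −0.03 | −0.7 × 0.15 = −0.105 |
| Persists, (1 − slope) × δ | 0.3 × 0.05 = 0.015 | 0.4 × 0.15 = 0.06 |

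A simulation of the fading case agrees with the formula. At δ = 0.10 and slope 0.6 it gave −0.058 against −0.06. At δ = 0.05 and slope 0.6 it gave −0.028 against −0.03.

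**Scale.** With no effect in never-takers, the ITT effect equals engagement × d:

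- 0.25 × 0.20 = 0.05
- 0.45 × 0.20 = 0.09
- 0.65 × 0.20 = 0.13

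The formula is that of Model A. In Models B and C the slopes are class-specific and class is latent in UC, so the error there will differ. The route is the same.

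**The case against.** The strongest reply is that harm needs disclosure before the answers, not just allocation before them. No sentence says when participants learn their arm. Credentials are issued at screening, and allocation and day 0 are adjacent columns. The sentence on FFW credentials lists everything they open over the whole study, so it sets no page order, and access from Time 1 could mean once the battery is done. Nor is the self-efficacy-to-comply item placed before the outcome scales. All this stands. Disclosure before Time 1 is a strong inference from the differing instructions and payments and the absence of stated participant blinding. It is not a stated fact.

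Three stronger readings are tempting, and the document supports none of them:

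- *People without Time 1 data are dropped.* The Data analytic approach says missing data are handled under missing at random, and no exclusion is stated. The Time 1 payment is $5 in both arms. Only the possibility of unequal loss remains.
- *The treatment effect is biased by a known amount or in a known direction.* Both depend on δ, the slope and persistence. The comparison above also uses the smallest effect the plan models. At d = 0.50 the ITT effect is already 0.125 to 0.325 SD (0.25 × 0.50 to 0.65 × 0.50).
- *Every model is affected.* Time 1 adjustment is stated for Models A and B and inherited by C. The exploratory path model is not described at that level.

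One might also say that an article leaves page order to the full protocol. That covers when the challenges unlock. It does not cover allocation before the battery, which this article fixes itself.

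**Conclusion.** The concern holds as a design weakness in the stated sequence. The document puts allocation before a self-reported baseline that Models A to C then adjust for, and describes no earlier measure of any primary outcome. Participants can probably know their arm when they answer, and FFW participants may have seen introductory content.

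The possible error is −0.03 to about −0.10 SD if the shift fades, or 0.015 to 0.06 SD in the direction of the shift if it persists fully. This rests on a positive shift of 0.05 to 0.15 SD and a slope of 0.6 to 0.7, both assumed. That is comparable with the 0.05 to 0.13 SD ITT effect for a small complier effect, and minor against a large one. The document does not establish that the bias occurs.

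**What to change.** Run consent, then the full Time 1 battery, then allocation and disclosure, and open FFW challenge access only once the battery is submitted. Keep the self-efficacy-to-comply item after the introductory challenges, shown separately from the Time 1 scales. Amend Table 1 and the Usual care and Fun for wellness sections to match. If this was already the real order, correct those places to say so. Table 1 should not be reordered unless the procedure is, or already was, in that order.

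The cost is a change in the order of web pages, with no extra contact. People who do not finish the battery are simply not randomised. The change makes the expected Time 1 difference between arms zero. It does not remove a reaction to arm in the self-reports at follow-up, which is a separate matter.

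Enrolment was scheduled to begin on 8 August 2018. If it has begun under the stated order, report Time 1 completion and Time 1 means by arm, keep all randomised participants in the analysis, and show results with and without Time 1 adjustment as a sensitivity check. Say plainly that neither version can be taken as free of bias if disclosure preceded Time 1: a shift that fades distorts the adjusted estimate, and one that persists enters the unadjusted estimate in full.
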